#### Analysis

Apart from patients that will have to be excluded because of noncompliance as described above, or patients who had to undergo emergency deblinding due to serious medical adverse events, intention to treat analysis will be performed. Multi Level Analysis will be performed which will allow us to correct for variance associated with the different sites in this Multisite RCT. Effect sizes will be estimated in terms of Cohen's d and regression analysis will be performed. Possible confounders such as age, gender, immigrant status, level of education, history of treatment and life events will be included as covariates in the analysis. An independent Helmert analysis will be performed with the following contrasts: Duloxetine alone versus TCCCL + duloxetine and TCCCL + placebo; and then TCCCL + duloxetine versus TCCCL plus placebo.

To assess the cost effectiveness, we will apply a cost-utility analysis. The results will be expressed as cost per QALY. The economic evaluation will be undertaken from a societal perspective. Hence, all relevant effects and costs due to resource utilisation within the healthcare (direct medical costs) and costs due to production losses (productivity costs) will be included.

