### Treatment allocation and blinding

This is a placebo controlled double blind study for the medication part of the study, which means that the allocation of duloxetine/placebo in the collaborative care arm is blinded.

Patients visiting the three participating Mental Health Institutions will be randomly assigned to one of the three treatment groups. Collaborative care and Duloxetine alone will be administered in a non-blind fashion. Administration of medication within the collaborative care conditions will be double blind and placebo controlled. Outcome assessments will be performed by a blinded research assistant.

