### Emergency deblinding

Emergency deblinding of the medication condition is performed by telephone to a research associate who is not involved in treatment procedures. This happens in case of serious adverse medical events. Subjects, who are deblinded before the end of the treatment procedures, will not be incorporated in the final analysis. In case of emergency deblinding or non-compliance, the code of medication (duloxetine or placebo) in the collaborative care groups will be broken. In case of duloxetine, the medication will be reduced and stopped according to protocol. All the remaining medication of this patient will be asked back and stored in a closed cabinet, separately from the rest of the study medication. In case of non-compliance, the patient will be excluded from this study and the final analysis.

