### Exclusion of the study during the intervention phase

Non-compliance is defined as not having used at least 80% of the prescribed medication (duloxetine/placebo) or no show on more than 20% of the appointments made with the psychiatrist or care-manager. The psychiatrist uses pill counts at every session to check if at least 80% of the pills have been used.

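### The analysis labelled intention to treat removes patients on post-randomisation events, and one of its two exclusions can occur only in the collaborative care arms

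*Protocol article*

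**What the plan says.** The Analysis section states that "intention to treat analysis will be performed", but opens that sentence with an exception: "Apart from patients that will have to be excluded because of noncompliance as described above, or patients who had to undergo emergency deblinding".

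The Emergency deblinding section makes both removals explicit. For deblinding: "Subjects, who are deblinded before the end of the treatment procedures, will not be incorporated in the final analysis". The trigger is given there too: "This happens in case of serious adverse medical events". For compliance: "In case of non-compliance, the patient will be excluded from this study and the final analysis".

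The section on exclusion during the intervention phase defines non-compliance as either of two things: using less than 80% of the prescribed duloxetine or placebo, or "no show on more than 20% of the appointments made with the psychiatrist or care-manager".

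On which arms have a blind, the Emergency deblinding section says that "the code of medication (duloxetine or placebo) in the collaborative care groups will be broken", and Treatment allocation and blinding says: "Collaborative care and Duloxetine alone will be administered in a non-blind fashion". Under Intervention, patients on duloxetine alone see only the psychiatrist. The article describes no analysis of all randomised patients.

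**The concern.** Intention to treat protects a comparison because group membership is fixed by randomisation. Here membership of the analysis set depends on pill use, attendance and serious adverse events, all of which come later and can be influenced by treatment.

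Compliance is the clearest case. Item 7 of the collaborative care description sets out contracting, psycho-education and frequent follow-up to improve adherence, and the third arm receives none of the collaborative care components. Excluding on compliance therefore conditions on something that the intervention is designed to change.

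The contrasts at stake are the two Helmert contrasts on PHQ-9 (duloxetine alone against both collaborative care arms, then duloxetine against placebo within collaborative care), the pain result and the cost per QALY. The last would leave out patients who stop treatment or have serious events, whose costs and utilities belong in the comparison. The Discussion also presents the trial as evaluating duloxetine in a real-life setting, which a set restricted to compliers does not do.

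**Working it through.** **1. The plan's own figures.** The Sample size section gives 80% power, a standardised difference of 0.5, 63 per arm and a 20% loss. Alpha is not stated; I assume 5% two-sided.
- n per arm = 2 × (1.96 + 0.8416)² / 0.5² = 62.8, so 63. This reproduces.
- 63 / 0.8 = 78.75, so 79 per arm and 237 in total. This reproduces.

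None of these figures is contested. The point is the analysis set.

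**2. Which exclusions differ by arm, from the text.**

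| Rule | Collaborative care + duloxetine | Collaborative care + placebo | Duloxetine alone |
|---|---|---|---|
| Emergency deblinding | possible | possible | impossible (open) |
| Pill use under 80% | applies | applies | same wording |
| No-show over 20% | psychiatrist and care-manager visits | psychiatrist and care-manager visits | psychiatrist visits only |

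A serious adverse event that leads to deblinding removes a collaborative care patient. The same event on duloxetine alone removes nobody by this rule. Between the two collaborative care arms the rules are identical.

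**3. The no-show rule (assumed inputs).** Assume 6 psychiatrist visits, 6 care-manager visits in the collaborative care arms, and independent misses. Exceeding 20% means at least 2 of 6, or at least 3 of 12 if pooled.

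| Chance of missing a visit | Psychiatrist only (6) | Pooled (12) | Threshold per provider (6 + 6) |
|---|---|---|---|
| 5% | 3.3% | 2.0% | 6.4% |
| 10% | 11.4% | 11.1% | 21.5% |
| 15% | 22.4% | 26.4% | 39.7% |

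If the threshold applies per provider, collaborative care loses nearly twice as many. If visits are pooled, the difference is small and changes sign.

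**4. Size of bias (assumed inputs).** Let p be the fraction excluded in an arm and Δ the PHQ-9 gap, in SD, between excluded and retained patients, the same in each arm. Overall mean = retained mean + p × Δ, so the retained mean is too low by p × Δ and the contrast is biased by Δ × (p1 − p2).
- Smallest case: 0.5 × 0.10 = 0.05 SD.
- Largest case: 1.0 × 0.20 = 0.20 SD.
- With the article's SD of 7.6, these are 0.05 × 7.6 = 0.4 and 0.20 × 7.6 = 1.5 PHQ-9 points, against a planned 0.5 SD.
- At 50 per arm, SE = √(2/50) = 0.20 SD. The shifts are 0.25 and 1.0 SE, giving a type I error of 5.7% and 17.0%.
- If p1 = p2 with equal gaps, the bias is zero.

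**5. Cross-check with another model.** Let exclusion occur above a cut-off q of a normal propensity that has correlation ρ with PHQ-9. The retained mean shifts by −ρ × φ(q)/(1 − p). For the 1:2 contrast with 63 against 126, SE = √(1/63 + 1/126) = 0.154 SD.
- 20% against 10% removed: φ(q)/(1 − p) is 0.350 and 0.195. With ρ from 0.2 to 0.5 the bias is 0.03 to 0.08 SD and the type I error 5.5 to 7.9%.
- 30% against 10% removed: bias 0.06 to 0.15 SD, type I error 6.8 to 16.5%.

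Where excluded patients have worse PHQ-9 scores and collaborative care loses more of them, the bias favours collaborative care.

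**6. Power, if exclusions come on top of the 20% loss.** Two-sample t-test, 0.5 SD, two-sided 5%.
- 10% more excluded: 79 × 0.8 × 0.9 = 56.9 per arm. Pairwise power is 75.3%; the 1:2 contrast has about 86%.
- 20% more excluded: 79 × 0.8 × 0.8 = 50.6 per arm. Pairwise power is 70.2%; the 1:2 contrast has about 82%.

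**The case against.** The exclusions are disclosed in the same sentence as the label, so this can be called a pre-specified restricted set under the wrong name. That is fair as to openness, but the plan offers no other primary set, so the wrong name covers the only analysis described.

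Several stronger readings are tempting, and the article does not support them:

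- **That both rules are known to remove patients unequally.** Only the deblinding exclusion is one-sided by construction. The pill rule is worded alike for all arms, and the no-show rule reads naturally as one pooled fraction, for which more visits need not mean more exclusions.
- **That serious events or intolerance fall unequally on duloxetine and placebo.** This is plausible, but no rates by arm are given and the rules in those two arms are the same.
- **That all excluded patients lose their follow-up data.** Leaving the study is stated for non-compliers. For deblinded patients only removal from the final analysis is stated.
- **That the exclusions certainly add to the 20% loss.** The sample size is framed in completers, and an excluded patient might already count as a non-completer. The article does not settle this.
- **That the trial as a whole becomes underpowered.** The 1:2 contrast stays above 80% in the cases computed.

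What stands against the objection is that none of this restores the randomised groups. Nor can a statistical analysis plan be assumed to fill a gap here, because the protocol has already fixed the rule.

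**Conclusion.** The concern holds. The article fixes an analysis set defined by events after randomisation and calls it intention to treat. Three parts are firm because they rest on the text alone: the label is wrong, the deblinding exclusion cannot reach the duloxetine-alone arm, and excluding on compliance conditions on something collaborative care sets out to change.

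The size is not known. The range of 0.05 to 0.20 SD, with a type I error of about 6 to 17% at 50 per arm, depends wholly on an assumed 10 to 20 point difference in exclusion and an assumed gap of 0.5 to 1.0 SD. Milder assumptions give 0.03 to 0.08 SD, and equal removal with equal gaps gives none. The fall in power to about 70 to 75% concerns pairwise comparisons only, and only if exclusions of 10 to 20% come on top of the 20% loss.

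The plan should be changed whatever the true size, since the remedy is cheap and follow-up that is not collected cannot be recovered.

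**What to change.** - In Analysis, define the primary and the cost-utility analyses on all randomised patients in their allocated arm, and delete the exception for non-compliance and emergency deblinding.
- In Emergency deblinding, delete the two statements that remove these patients from the final analysis, and state that non-compliant patients stay in the study for measurement.
- Keep sending the scheduled T1 to T4 questionnaires to non-compliant and deblinded patients.
- Keep the 80% pill and 20% no-show definition for a per-protocol sensitivity analysis labelled as such, and say whether missed visits are pooled across psychiatrist and care-manager or counted per provider.

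No rule on clinical stopping or on deblinding has to change, and no sample size figure has to change. With outcomes on all 79 per arm, pairwise power at 0.5 SD would be at most about 88%. The cost is a few sentences and some extra questionnaire follow-up. The downside is that the estimated effect may be smaller than among compliers.

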#### Recruitment of care-managers and psychiatrists in the Mental Health Institutions

Care-managers and psychiatrists will be recruited at the three participating mental health centers (GGz Breburg, Arkin, GGz inGeest) and form treatment teams for the trial. The care-managers are psychiatric nurses or psychologists who receive training in care management (including PST) to provide in the collaborative care interventions. The psychiatrists are trained in prescribing duloxetine and placebo medications as well as the pain medication according to the algorithm and in writing a consultation letter for the general practitioner and patient. Psychiatrists are blinded for the antidepressant medication (duloxetine/placebo), but not for the pain medication. Pain medication management will be provided by the psychiatrists in the duloxetine and placebo arm with collaborative care, but not in the treatment arm with duloxetine alone. In this study, care-managers and psychiatrists work according to a 'Case Registration Form' (CRF). In this CRF all the steps are described that a care-manager/psychiatrist has to do during an appointment with a patient.

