#### Intervention

##### First and second design arm: Duloxetine/placebo plus collaborative care

This intervention contains collaborative care, duloxetine or placebo, and pain medication according to an algorithm. Collaborative care will be provided within a multidisciplinary team comprising of a care-manager, psychiatrist and a physiotherapist. They all will apply treatment simultaneously according to protocol. Only patients in the collaborative care arms will receive treatment of all three specialists. The patients in the Duloxetine alone arm will only receive treatment of the psychiatrist.

The GP of the patient will be informed of the participating of the patient. Also, GP's in the same areas as the mental health centers will receive information about the study and are asked to refer patients if they have the complaints under study. The interventions will be monitored every two weeks and when needed, the doses of medication can be raised according to the algorithm shown in Figures 2 and 3. The minimum duration of the interventions will be 12 weeks. The medication blinding code will be broken after 12 weeks. A maximum of 2 sessions will follow to end the treatment. After this, medication and follow up treatment will be handed over to the GP. In case of treatment response (50% reduction on the initial score), but non-remission, as indicated by a score of > 5 on the PHQ-9 after 12 weeks, the patient will be referred back to the GP with subsequent antidepressant treatment and pain medication advice.

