### Sample size

#### Sample size for severity of depression as primary outcome

In a former RCT on collaborative care performed in the primary care setting, the effect size of a collaborative care intervention versus no such intervention as measured by PHQ-9 was 4.64/7.6 = 0.6 (the SD on the endpoint PHQ-9 varied between 7.0 and 8.3) [104]. In this study, we compare collaborative care plus duloxetine and collaborative care plus placebo versus the monotherapy duloxetine alone, and we compare collaborative care plus duloxetine versus collaborative care plus placebo. To have a minimum power of 80% to detect a standardized difference of 0.5 a minimum of 63 patients per arm is needed, that is 189 completers. In order to anticipate for possible loss to follow up of 20%, 3 × 79 (237) patients will be included [105].

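### Site is the only clustering level named; care-manager clustering, present only in the collaborative care arms, can make the interval for collaborative care versus duloxetine alone too narrow

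*Protocol article*

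**What the plan says.** The Analysis section commits to a multilevel model and gives its purpose in one sentence: "Multi Level Analysis will be performed which will allow us to correct for variance associated with the different sites in this Multisite RCT". No care-manager, physiotherapist or psychiatrist level is mentioned.

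The same section fixes the contrasts: "Duloxetine alone versus TCCCL + duloxetine and TCCCL + placebo; and then TCCCL + duloxetine versus TCCCL plus placebo".

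On who treats whom:

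- Section on recruitment of care-managers and psychiatrists: "Care-managers and psychiatrists will be recruited at the three participating mental health centers".
- Section on the first and second design arms: "Only patients in the collaborative care arms will receive treatment of all three specialists". It continues: "The patients in the Duloxetine alone arm will only receive treatment of the psychiatrist".
- Section on the third design arm: problem solving treatment, guided self-help, pain medication, physiotherapy and the consultation letter are all withheld in that arm.
- Treatment allocation and blinding: "Administration of medication within the collaborative care conditions will be double blind and placebo controlled".

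The sample size section states: "To have a minimum power of 80% to detect a standardized difference of 0.5 a minimum of 63 patients per arm is needed". It contains no design effect.

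**The concern.** The care-manager delivers problem solving treatment, guides the self-help manual, monitors symptoms and refers to the physiotherapist. Skill and style at these tasks differ between care-managers, so patients who share one may have correlated PHQ-9 outcomes. This correlation arises in two arms and has no counterpart in the third. It sits within site, so a site term does not remove it.

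At stake is the comparison of collaborative care with duloxetine alone. It is the first Helmert contrast, and the stated hypothesis also includes the pairwise comparison of combined treatment with duloxetine alone. A standard error that leaves out care-manager variance is too small, and the error favours declaring a collaborative care effect that is not there.

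**Working it through.** **Inputs from the article.** Three sites; 63 completers per arm; standardized difference 0.5; power 80%; 20% loss; contrasts as quoted. **Assumed, because the article does not give them:** two-sided alpha 5%; *m* = 5 to 10 patients per care-manager per arm (63/10 to 63/5, about 6 to 13 care-managers in total); care-managers shared by both collaborative care arms; ICC 0.02 to 0.05; total variance 1 in every arm.

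**The plan's own figure.** n per arm = 2 × (1.960 + 0.842)² / 0.5² = 62.8, so 63. With 20% loss, 63/0.8 = 78.75, so 79 per arm and 237 in total. Both match the article, and both treat patients as independent.

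**First Helmert contrast (126 versus 63).** Each care-manager has 2*m* patients across the two collaborative care arms, so DE = 1 + (2*m* − 1) × ICC.

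- Variance under independence: 1/126 + 1/63 = 3/126. Power at 0.5 SD: 0.5/√(3/126) = 3.240, and Φ(3.240 − 1.960) = 90.0%.
- True variance: DE/126 + 1/63 = (DE + 2)/126, so the variance ratio is VR = (DE + 2)/3.
- Type I error of the site-only model: 2 × [1 − Φ(1.960/√VR)].
- Power with a correct standard error: Φ(3.240/√VR − 1.960).

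**Pairwise contrast, collaborative care with duloxetine versus duloxetine alone (63 versus 63).** DE = 1 + (*m* − 1) × ICC and VR = (DE + 1)/2. The value 0.5/√(2/63) = 2.806 replaces 3.240, and power under independence is 80.1%.

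| Contrast | *m* per arm | ICC | DE | VR | Type I error, site-only model | Power, correct SE |
|---|---|---|---|---|---|---|
| Helmert 1 | 5 | 0.02 | 1.18 | 1.060 | 5.7% | 88.2% |
| Helmert 1 | 10 | 0.05 | 1.95 | 1.317 | 8.8% | 80.6% |
| Pairwise | 5 | 0.02 | 1.08 | 1.040 | 5.5% | 78.6% |
| Pairwise | 10 | 0.05 | 1.45 | 1.225 | 7.7% | 71.8% |

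The last two columns belong to different analyses. The inflated type I error comes from the model that leaves out care-manager, and the lower power from the model that includes it. The power of the site-only model is Φ((2.806 − 1.960)/√VR) for the pairwise contrast, that is 79.7% and 77.8%.

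**Does a site term absorb the clustering?** This was simulated with 20,000 trials per setting, site as a fixed effect, *K* care-managers in total nested in site, and care-managers shared by both collaborative care arms. Type I error for the first Helmert contrast was:

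- *K* = 18, ICC 0.02: 5.4%
- *K* = 9, ICC 0.05: 7.4%
- *K* = 6, ICC 0.10: 13.4%

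So it does not.

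**Second Helmert contrast.** With shared care-managers their effects cancel between the two arms: true variance 2(1 − ICC)/63 against 2/63 in the model. At ICC 0.05 the ratio of true to model standard error is √0.95 = 0.975. Simulated type I error was 4.0% to 4.8%. This interval is not too narrow.

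**Ends of a wider range.** For the first Helmert contrast, 18 care-managers and ICC 0.01 raise the standard error by 1%. Six care-managers and ICC 0.10 raise it by 29%.

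**The case against.** The strongest objection is that this rests on one sentence in a condensed article. The sentence does not say that site is the sole level, that patients within a site are treated as independent, or that the care-manager goes unrecorded. The full protocol or an analysis plan may add a provider level. That stands as a limit on wording: site is the only level *named*. A reader might infer that the trial team has decided to ignore care-managers, and the article does not support that. It does not remove the point, because the article chose to state what the multilevel analysis corrects for, and what it states does not cover the clustering that differs between arms.

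A second objection is that the size depends on two quantities the article does not give. That also stands. A reader might infer that the intervals *are* too narrow and that power falls below plan. The article supports neither as fact. With a small ICC or caseload the effect is negligible, and over the assumed range the first Helmert contrast keeps at least 80% power with a correct standard error. Only the pairwise contrast falls below 80%.

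Third, a reader might object that three sites leave 2 degrees of freedom for a between-site variance. That adds little. Patients are randomized individually, so if all three arms run in each site, a common site effect largely cancels from the treatment contrasts. The article also does not say that site is random.

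Finally, physiotherapists also treat only the collaborative care arms, and psychiatrists treat all three arms. Modelling the care-manager alone is a choice. It is defensible because the care-manager delivers most of the added components, but the plan should say how the other providers are handled. A care-manager random effect will itself be imprecise if care-managers are few.

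**Conclusion.** The point holds in conditional form. The article names site as the only source of clustering to be corrected for, and its design puts care-manager clustering in two of three arms. If the care-manager ICC is positive, a site-only model understates the standard error for collaborative care versus duloxetine alone, in both the first Helmert contrast and the pairwise comparison.

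Under the assumptions listed in the working, nominal 5% error becomes 5.7% to 8.8% (Helmert) or 5.5% to 7.7% (pairwise). The cost in power once the standard error is correct is from 90% to 88%–81%, or from 80% to 79%–72%. The comparison of duloxetine with placebo within collaborative care is not affected in the harmful direction if the same care-managers serve both arms. Blinding makes that likely, but the article does not state it.

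This is a moderate point, worth settling before analysis because the identifier it needs is best captured during treatment.

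**What to change.** In the Analysis section:

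1. Fit site as a fixed effect (two indicators).
2. Add a care-manager random effect that applies only in the two collaborative care arms (a partially nested model), with small-sample degrees of freedom.
3. Record the care-manager identifier for every collaborative care patient.
4. State the expected number of care-managers, whether they serve both collaborative care arms, and the ICC assumed. Say how physiotherapists and psychiatrists are treated in the model.

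The cost is a few lines of text and one variable. The price in precision is slightly wider intervals for the collaborative care contrast, more so if care-managers are few. The contrast between the two collaborative care arms loses nothing if care-managers are shared.

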#### Recruitment of patients

All the patients that are referred to the participating mental health centers are screened for depressive symptoms and pain complaints. This study will focus on patients with a depressive disorder and (sub)chronic pain complaints. Sub chronic pain is defined as pain of ≥ 6 weeks and chronic pain is defined as pain with a duration of at least 12 weeks. Consecutive patients that present themselves at the special mental health outpatient clinic will be screened for MDD and concomitant pain of ≥ 6 weeks duration with a questionnaire.

This questionnaire will consist of the PHQ-9 [13] and the item on 'average pain' from the BPI [79], that will be used as a screener for respectively depressive disorder and (sub)chronic pain symptoms. Also, the patient will receive an informed consent form with information about the study. Patients are eligible for the study if they have a score of 10 or more on the PHQ-9 and a score of 3 or more on the 'average pain' item of the BPI. When a patient screens positive on the questionnaires mentioned above, the patient will receive a telephonic interview in which a MINI interview will be administered in order to clinically confirm the diagnosis MDD and to confirm that the patient suffers from (sub)chronic pain. In that case, he or she will receive additional information about the treatment part of the study and will be asked if he or she is willing to participate. When the patient is willing to participate, the patient is included in the study. A baseline questionnaire with second informed consent form, for the treatment part of the study, will be sent to the patient’s home address or made available on a secured website. After completion of the baseline questionnaire, the patient will be randomized in one of the three interventions.

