#### Data collection

Measurement will take place at baseline (T0), and three, six, nine and twelve months after baseline, respectively T1, T2, T3 and T4.

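### The named covariates for the primary PHQ-9 analysis do not include the baseline PHQ-9 score, so the plan does not secure the precision that score offers

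*Protocol article*

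**What the plan says.** The covariates are given in the Analysis section of the protocol article: "Possible confounders such as age, gender, immigrant status, level of education, history of treatment and life events will be included as covariates". The same section describes the model only by its treatment of site: "Multi Level Analysis will be performed which will allow us to correct for variance associated with the different sites in this Multisite RCT".

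Two other places list variables for the analysis. The controlling variables under Outcome parameters name demographics, pain classification and somatic comorbidity as effect modifiers. Controlling variables in analysis adds comorbid mental disorders measured with the PHQ (anxiety is the example) and hypochondriac tendencies. The depression severity score at baseline is in none of the three lists.

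That score should be available. Data collection says: "Measurement will take place at baseline (T0), and three, six, nine and twelve months after baseline". The Abstract counts depression among the data collected at baseline. Recruitment of patients puts this before allocation: "After completion of the baseline questionnaire, the patient will be randomized in one of the three interventions".

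The primary outcome is PHQ-9 severity (Primary outcome parameter). The Hypothesis section speaks instead of a reduction in symptoms on the PHQ-9, and the Sample size section works on the endpoint scale: "the SD on the endpoint PHQ-9 varied between 7.0 and 8.3".

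**The concern.** In a randomised trial, baseline variables are not confounders in the usual sense, because allocation is independent of them by design. A covariate earns its place by explaining variation in the outcome, and the baseline value of the outcome is usually the strongest candidate. A list chosen as possible confounders follows a different principle: it names demographics, treatment history and life events, and does not name the variable most likely to help.

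The article also leaves open how T0 is used. The primary analysis could compare endpoint scores, compare changes, treat T0 as the first repeated measure, or adjust for T0. These choices differ in precision. At stake is the width of the confidence interval and, with it, the power of the contrasts, above all the one between the two collaborative care arms, which has the fewer patients.

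**Working it through.** **Inputs from the Sample size section.** "To have a minimum power of 80% to detect a standardized difference of 0.5 a minimum of 63 patients per arm is needed". Significance level and sidedness are not stated there; I assume two-sided 5%.

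**Input not in the document.** The correlation r between baseline and endpoint PHQ-9. I show 0.2 to 0.5. Entry requires a PHQ-9 of 10 or more, which narrows the baseline range and may pull r toward the lower end.

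**Step 1: reproduce the plan's figure.** Normal approximation, n per arm = 2(1.960 + 0.842)² / 0.5² = 62.8, rounded up to 63. Power at 63 per arm is 80.1% by the normal approximation and 79.5% by the noncentral t distribution. The plan's number therefore reproduces with no baseline adjustment. The remaining steps are t-based throughout.

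**Step 2: effect of adjustment.** With baseline as a covariate, the residual SD is multiplied by √(1 − r²), so the effective standardised difference is 0.5/√(1 − r²). The Helmert analysis has two contrasts:

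- Collaborative care + duloxetine versus collaborative care + placebo, 63 versus 63: noncentrality = effective difference × √(63 × 63/126) = effective difference × √31.5.
- Duloxetine alone versus both collaborative care arms, 63 versus 126: noncentrality = effective difference × √(63 × 126/189) = effective difference × √42. The same difference of 0.5 is assumed here.

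| Assumed r | Residual variance removed (r²) | SE multiplier | Effective difference | Power, 63 v 63 | Power, 63 v 126 |
|---|---|---|---|---|---|
| no adjustment | 0% | 1.000 | 0.500 | 79.5% | 89.7% |
| 0.2 | 4% | 0.980 | 0.510 | 81.1% | 90.8% |
| 0.3 | 9% | 0.954 | 0.524 | 83.1% | 92.2% |
| 0.4 | 16% | 0.917 | 0.545 | 86.0% | 94.0% |
| 0.5 | 25% | 0.866 | 0.577 | 89.5% | 96.1% |

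The one degree of freedom spent on the covariate is ignored; it is immaterial at these sizes.

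**Step 3: why it helps to state how T0 is used.** If the reduction in the hypothesis were analysed as an unadjusted change score, with equal baseline and endpoint variances (assumed), the SD would be multiplied by √(2(1 − r)). Power for 63 versus 63 would then be 65.3% at r = 0.3, 72.0% at r = 0.4 and 79.5% at r = 0.5. If the entry threshold makes the baseline SD smaller than the endpoint SD, the change score does less badly than this. Adjustment for T0 is at least as precise as either unadjusted analysis.

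**The case against.** The strongest reply is that silence is not exclusion. The list opens with the words such as, so it is not closed, and no sentence says that T0 will be left out. A multilevel model over five time points may carry T0 as its first measurement, and the hypothesis and the response definition (a 50% reduction) both refer back to baseline. An article may leave such detail to a full protocol or analysis plan that is not shown here. All of this stands. A reader might infer that the plan drops the baseline score and throws precision away, or that chance imbalance in severity will pass straight into the estimate. The document does not support either reading. The second would need an endpoint-only model without T0, which is not what the article specifies.

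It also stands that there is no defect of validity or of planned power: randomisation keeps the unadjusted comparison unbiased, and 63 per arm does not lean on a covariate. The gain is uncertain as well. At r = 0.2 it is under 2 percentage points for either contrast, and the contrast against both collaborative care arms starts near 90%.

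A reader might further infer that adjustment would make good the difference between the two enrolment targets in the article (219 and 237). That is a separate discrepancy, and an assumed correlation does not settle it.

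What the reply does not remove is that the article does choose to name its covariates, selects them as confounders, and names the baseline outcome in none of three lists. That is more than detail left for later.

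**Conclusion.** The point holds as a matter of efficiency. The plan names covariates for the primary analysis without securing the one most likely to reduce residual variance, and does not say how T0 enters the model. The benefit of naming it is a rise in t-based power from 79.5% to 81–90% for collaborative care with duloxetine versus with placebo, and from about 90% to 91–96% for duloxetine alone versus both collaborative care arms. These ranges rest on r between 0.2 and 0.5, two-sided 5%, a standardised difference of 0.5 for each contrast, and 63 completers per arm. None of them implies that the trial is biased or that its stated 80% power is wrong.

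**What to change.** Add one sentence to the Analysis section: the primary multilevel model includes the T0 PHQ-9 score, either as a fixed covariate or through a baseline mean constrained to be equal across arms, and the model for the BPI likewise includes T0 BPI. Specify this before any outcome data are analysed. That is a better marker than deblinding, because each patient is deblinded individually after 12 weeks and there is no single date. The existing site adjustment and listed covariates can stay as they are.

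The cost is one sentence. T0 is already a measurement point, and the sample size need not change.
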